# *Yukmijihwang-tang* for the treatment of xerostomia in the elderly: study protocol for a randomized, double-blind, placebo-controlled, two-center trial

**DOI:** 10.1186/1745-6215-14-281

**Published:** 2013-09-03

**Keywords:** Xerostomia, *Yukmijihwang-tang*, *Yin-Deficiency*, Visual analogue scale

## Abstract

**Background:**

Xerostomia, a subjective sense of dry mouth, is not generally regarded a disease despite its high prevalence among the elderly, and therefore continues to impair affected patients’ quality of life. In traditional Korean medicine, ‘*Yin-Deficiency*’ has been implicated in the pathogenesis of xerostomia among the elderly. *Yukmijihwang-tang* is a famous herbal prescription used to relieve ‘*Yin-Deficiency*’, and reportedly has antioxidant effects; therefore, it is postulated that *Yukmijihwang-tang* can be used to treat xerostomia in the elderly. However, to our knowledge, no clinical trial has been conducted on the effects of *Yukmijihwang-tang* on xerostomia. Thus, we designed a randomized clinical trial to investigate the effects and safety of *Yukmijihwang-tang* on xerostomia in the elderly. In addition, we will clarify the aforementioned assumption that ‘*Yin-Deficiency*’ is the major cause of xerostomia in the elderly by identifying a correlation between xerostomia and ‘*Yin-Deficiency*’.

**Methods/Design:**

This randomized, double-blind, placebo-controlled trial will be carried out at two centers: Kyung Hee University Korean Medicine Hospital and Kyung Hee University Hospital at Gangdong. We will recruit 96 subjects aged 60-80 years who have experienced xerostomia for 3 months prior to participation. Subjects who present with score >40 on the visual analogue scale for xerostomia and unstimulated salivary flow rate under 0.3mL/min will be included and the randomization will be carried out by an independent statistician by using a random number creation program. The subjects and all researchers except the statistician will be blinded to the group assignment. *Yukmijihwang-tang* or placebo will be administered to each group for 8 weeks. The primary outcome is change in the scores for the visual analogue scale for xerostomia and the dry mouth symptom questionnaire from 0 to 8 weeks.

**Discussion:**

It will be assessed whether *Yukmijihwang-tang* can be used as a new herbal treatment for xerostomia in the elderly by demonstrating its therapeutic effects in a well-designed clinical trial.

**Trial registration:**

ClinicalTrials.gov Identifier:
NCT01579877

## Background

Xerostomia, which is a subjective sense of oral dryness
[1], is a fairly common condition among the elderly
[2]. It is estimated that approximately 30% of the population aged 65 years and older have xerostomia
[3], and several studies have reported a higher prevalence in the elderly than in the younger population
[4-7].

The causes of xerostomia are long-term uses of xerostomia-inducing medications for chronic diseases and systemic diseases (for example, Sjögren’s syndrome, diabetes mellitus, Alzheimer’s disease, and Parkinson’s disease), head and neck radiation therapy, aging, heavy smoking, and stress
[8]. In the elderly, the long-term use of medications and aging are regarded as major causes of xerostomia
[9]. However, recent xerostomia studies mostly focused on Sjögren’s syndrome or postradiotherapy-induced xerostomia, which are related to salivary gland damage, and only a few studies have assessed xerostomia in elderly subjects who did not exhibit obvious structural damage of the salivary glands
[10,11].

Xerostomia is not generally accepted as a disease despite its high prevalence in the elderly; therefore, this condition continues to impair the affected patient’s quality of life (QoL)
[7,12]. For example, xerostomia in the elderly is known to cause dental problems and changes in chewing, swallowing, digestion, and taste
[12]. Therefore, many xerostomia patients turn to solutions such as frequent water intake, sour foods, and alternative therapies (herbs or nutritional supplements)
[13]. However, it is unclear whether these behaviors or therapies provide relief from xerostomia symptoms.

In traditional Korean medicine (TKM), ‘*Yin-Deficiency*’ is regarded as the main pathologic cause of xerostomia in the elderly
[14]. Generally, the balance of *Yin* and *Yang* is important for maintaining health and treating diseases in TKM
[14]. Particularly, *Yin* in ‘*Yin-Deficiency*’ refers to general body fluids, including blood, and *Jing* (mostly translated as ‘essence of body’)
[15]. Therefore, ‘*Yin-Deficiency*’ is closely correlated with a shortage of body fluids, which results in various symptoms (dry mouth, dry eyes, or constipation)
[14]. TKM has many herbal prescriptions for treating ‘*Yin-Deficiency*’
[10,16].

*Yukmijihwang-tang* (YMJ; *Liu-wei-di-huang-tang* in traditional Chinese medicine; *Lokumijio-to* in Kampo Medicine) is described in the ancient Chinese literature, ‘*Key to Therapeutics of Children’s Diseases*’
[17], and is composed of six herbs. It has long been used for enriching the fluid-humor of the body in TKM, and it can treat *Deficiency Fire Flaming Upward* due to ‘*Yin-Deficiency*’. Recently, many studies have described the pharmacological effects of YMJ, such as protection against renal ischemia/reperfusion in rats
[18], memory enhancement in rats
[19], and antioxidant and antidiabetic effects in early diabetic nephropathy patients
[20]. In xerostomia-related aspects, YMJ is a famous herbal formula for body enrichment, which includes relieving ‘*Yin-Deficiency*’
[21], because of its demonstrated antioxidant and free radical scavenging activities in animal studies
[18,22]. Thus, it is postulated that YMJ can improve xerostomia in the elderly by enriching the *Qi* of the body and tonifying *Yin*.

However, to our knowledge, no clinical trial has examined the effects of YMJ on xerostomia. Therefore, we designed a randomized clinical trial to assess the effects and safety of the use of YMJ on xerostomia in the elderly. To evaluate any changes in xerostomia symptoms, the visual analogue scale (VAS) for xerostomia and the salivary flow rate will be analyzed.

## Methods/Design

### Objectives

The aims of this study are to:

(1) obtain clinical evidence regarding the safety and effects of YMJ in elderly individuals with xerostomia;

(2) identify a correlation between xerostomia in the elderly and the ‘*Yin-deficiency*’ state.

### Hypothesis

We hypothesize that 8 weeks of YMJ administration will improve xerostomia in the elderly and will not induce severe side effects.

### Design

This is an academic research study that will be conducted as a randomized, placebo-controlled, double-blind, two-center trial at Kyung Hee University Korean Medicine Hospital and Kyung Hee University Hospital at Gangdong in Seoul, Korea.

This clinical trial will consist of an 8-week oral administration of YMJ with two visits at 4-week intervals and a 2-week follow-up period. Before enrollment, all subjects will go through a 7-day run-in period.

After randomization, all subjects will be divided into two groups: the YMJ and placebo groups. Each group will be provided with YMJ or a placebo for 8 weeks and the subjects will be required to take 3 g of YMJ or placebo three times a day. During the 8-week administration period, subjects will be prohibited from taking any kind of xerostomia-relieving drug such as pilocarpine or cevimeline. Primary and secondary outcomes will be measured at baseline and at 4 weeks, 8 weeks, and 10 weeks after randomization.

The flow of the entire trial is shown in Figure 
1.

**Figure 1 F1:**
[figure not shown]
Flow chart of the study.

### Sample size calculation

The formula for estimating the sample size is as follows:

$$n_{t}=n_{c}=\left\{{\left(Z_{\alpha }{}_{/2}+Z_{\beta }\right)}^{2}\sigma^{2}\left(\lambda +1\right)/\lambda \right\}/{\left(\mu_{c}-\mu_{t}\right)}^{2}$$

A previous study demonstrated 1.54 points of improvement (*μ*_c_ - *μ*_t_= *Δ*) in the VAS for xerostomia after 4 weeks of treatment compared to that demonstrated after the placebo treatment
[23]. The same study indicated a mean standard deviation (SD = *σ*) of 1.87. In our study, the ratio (*λ*) of the experimental group to the placebo group will be 1:1. With a power of 80% (1 - β) and a significance level of 5% (α), assuming Δ = 1.54 and σ = 1.87, a sample size of n_t_ = n_c_= 36 subjects per each group will be required (*n*_t_, number of YMJ group; *n*_c_, number of placebo group). Considering an assumed dropout rate of 25%, a total of 96 subjects will be needed. Although the intervention period in this study is different from that in previous similar study, we chose data from a previous study
[23]. The rationale for choosing these data is the lack of studies or guidelines that used the same herbal prescription (YMJ) or the same outcome measure as this study.

On the other hand, to our knowledge, no clinical study has been conducted to assess the correlation between xerostomia in the elderly and the ‘*Yin-deficiency*’ state. Thus, the current trial is regarded as a pilot study to assess this correlation. This correlation will be assessed with a sample size of 96 subjects, which we believe is an appropriate sample size for evaluating this clinical correlation. The results will be shown by using descriptive statistical analysis.

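### The sample-size formula and inputs as printed give 24 per group, not 36, so 36 per group and 80% power cannot both follow from the stated assumptions

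*Protocol article*

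**What the plan says.** The protocol article, under Sample size calculation, gives the normal-approximation formula for comparing two means, with the critical value taken at α/2. The inputs are all stated:

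- "With a power of 80% (1 - β") and "a significance level of 5% (α")
- "assuming Δ = 1.54 and σ = 1.87", the difference and SD being taken from an earlier placebo-controlled study of 4 weeks' treatment
- a ratio "of the experimental group to the placebo group will be 1:1"

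From these it concludes that "36 subjects per each group will be required". It then goes on: "Considering an assumed dropout rate of 25%, a total of 96 subjects will be needed".

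**The concern.** Formula, inputs and result stand together in one section, so the result can be checked by substitution, and it does not come out. The figure of 36 is about half as large again as the formula yields, which is too far off for rounding or a small-sample correction.

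This calculation is the only quantitative justification for the size of the trial. If the printed difference and SD are right, the stated power is too low and the trial recruits more people aged 60 to 80 than its own reasoning calls for. If 80% power is right, at least one printed input is wrong, and the effect the trial was designed to detect is not the one reported. The document does not let a reader choose between these.

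**Working it through.** **Inputs**, all from Sample size calculation: α = 0.05, two-sided because the formula uses the value at α/2; power 0.80; Δ = 1.54; σ = 1.87; λ = 1; dropout 25%.

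**The plan's own formula.** n per group = (Z_α/2 + Z_β)² × σ² × (λ + 1)/λ ÷ Δ²

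- (1.960 + 0.8416)² = 7.849
- σ² = 1.87² = 3.4969
- (λ + 1)/λ = 2
- Δ² = 1.54² = 2.3716
- n = 7.849 × 3.4969 × 2 ÷ 2.3716 = 23.15, so **24 per group**

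The stated 36 is not reproduced. An exact t-test calculation (noncentral t) gives 25: power is 79.8% at 24 per group and 81.4% at 25.

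**Can another setting give 36?** Difference and SD are held at 1.54 and 1.87.

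| Setting | n per group |
|---|---|
| As stated | 24 |
| One-sided 5%, 80% power | 19 |
| Two-sided 5%, 85% power | 27 |
| Two-sided 5%, 90% power | 31 |
| Two-sided 5%, 95% power | 39 |
| α 0.025, 80% power | 29 |
| α 0.025, 90% power | 37 |
| α 0.01, 80% power | 35 |
| Allocation factor 3 instead of 2 | 35 |
| SD multiplied by √2 | 47 |
| Allowance for a Wilcoxon test | about 25 to 27 |

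None gives 36. The three that come close (35, 35 and 37) need an α, power or allocation other than those stated.

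**What 36 per group would mean**

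- Power at the stated inputs: Φ(1.54/1.87 × √(36/2) − 1.960) = Φ(3.494 − 1.960) = 0.937. The noncentral t gives 0.931.
- Difference detectable at 80% power with SD 1.87: 2.8016 × 1.87 × √(2/36) = 1.235. With the t-test it is 1.252.
- SD that would make 36 correct at 80% power with Δ = 1.54: 1.54 ÷ (2.8016 × √(2/36)) = 2.33. With the t-test it is 2.30.

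**Dropout step**

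- From the stated 36: 36/0.75 = 48 per group, total 96. This reproduces the plan's total.
- From 24: 24/0.75 = 32 per group, total 64.
- From 25: 25/0.75 = 33.3, so 34 per group, total 68.

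The planned total therefore exceeds what the printed inputs need by 96 − 64 = 32, or 96 − 68 = 28 by the t-test.

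**The case against.** The strongest reply is that the discrepancy is on the safe side. On the printed assumptions the trial has more power than claimed, and the endpoint, the analysis and enrolment all stand. It could be regarded as a reporting slip. That is fair as far as it goes: nothing here shows an underpowered trial. But the reassurance depends on 1.54 and 1.87 being the values actually used, and that is what the inconsistency puts in doubt. If the SD used was about 2.33, the power is 80% as stated and the printed SD is wrong.

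Two further limits should be granted. Only the inconsistency is established, not which element is at fault; a misreported α or allocation ratio is possible as well as the SD or the difference. And the reading of a null result will rest on the confidence interval for the observed difference, not on this planning calculation, so the error does not damage that inference.

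Three other explanations fail:

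- **Deliberate margin.** The section mentions the different treatment period and the correlation aim, but attributes no increase in n to either. It presents 36 as what the listed inputs require.
- **Misprint of 24.** The 36 is carried forward to 96.
- **VAS scale.** The inclusion criteria use a threshold of 4, while the primary outcome is defined on 0 to 100 mm. The formula depends only on Δ/σ, so a change of units applied to both cancels.

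**Conclusion.** The concern holds. The printed formula and inputs require 24 evaluable subjects per group (25 by exact t-test), against 36 stated. With 36 per group the power for a difference of 1.54 and SD of 1.87 is 93.7% by the normal approximation and 93.1% by the t-test; 80% power corresponds to a difference of about 1.23 to 1.25. The total of 96 is a correct inflation of 36 and not a second error.

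These figures rest on the plan's own two-sided 5% level, its difference and SD, 1:1 allocation and 36 evaluable per group. They make no allowance for any gain in precision from the planned ANCOVA, which the printed formula does not include either. The statement that sizes the trial is wrong as written and should be corrected, although on the printed inputs the error is conservative.

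**What to change.** Go back to the original calculation first and establish which values were used. Then correct the sentence in one of two ways:

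- **If 1.54 and 1.87 are confirmed:** keep 96 and state that 36 evaluable subjects per group give about 93% power for a difference of 1.54 with SD 1.87, or 80% power for a difference of about 1.25.
- **If another input was used** (for example an SD of about 2.33, or a different difference, α, power or allocation): state that value and its source, and check that the formula then returns 36.

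In either case, give the scale on which the difference and SD are expressed, since the primary outcome is defined in millimetres from 0 to 100. The cost is one corrected sentence, with no change to enrolment.

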### Inclusion and exclusion criteria

In general, the definition of elderly is used to describe people over the age of 60 years
[24]; in accordance, we will recruit subjects who are between 60 and 80 years of age and have experienced xerostomia for 3 months prior to participation. We have restricted the subjects’ ages to below 80 years because individuals over this age are considered to have lower eligibility in this study on the basis of the rationale that the incidence of disease is increased as an individual ages.Therefore, we set an upper limit of 80 years on the subjects’ ages by a consensus among geriatric disease specialists.

The subjects should present with VAS scores >4 for xerostomia 2 weeks before the study period. In addition, the unstimulated salivary flow rates of the subjects should be under 0.3 mL/min. The subjects must agree that they will not receive xerostomia-related treatments for 3 months after initiation of the study.

Subjects who report the following conditions will be excluded:

(1) a history of treatments for autoimmune diseases like Sjögren’s syndrome, rheumatism, or lupus;

(2) a history of craniocervical radiation therapy, organ transplantation, severe psychiatric illness, or major depression;

(3) the use of any other herbal prescriptions or nutritional supplements at the screening phase;

(4) the use of xerostomia-relieving medications (pilocarpine and cevimeline) or therapies for xerostomia (mouthwash, gum, and toothpaste for xerostomia).

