### Outcome measurement

#### Primary outcome

VAS for xerostomia was chosen as a primary outcome to evaluate the subject’s improvement regarding discomfort due to xerostomia (ranging from 0 mm as no xerostomia to 100 mm as the most severe xerostomia). The measurements of VAS will be carried out at screening, baseline, at 4 weeks, and 8 weeks during YMJ administration, and at the end of study (10 weeks after baseline). The change of VAS scores before and after intervention (from week 0 to week 8) will be compared between the YMJ and placebo groups.

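### The entry threshold on the primary-outcome VAS is >4 in the inclusion criteria and >40 in the Abstract, neither with a unit, on a scale defined only as 0-100 mm

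*Protocol article*

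**What the plan says.** The protocol article gives the symptom threshold for entry twice.

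- Inclusion and exclusion criteria: "The subjects should present with VAS scores >4 for xerostomia 2 weeks before the study period".
- Abstract, Methods/Design: "Subjects who present with score >40 on the visual analogue scale for xerostomia".

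Neither figure has a unit. The scale is defined in one place only, under Primary outcome: "ranging from 0 mm as no xerostomia to 100 mm as the most severe xerostomia". The same section makes this VAS the endpoint ("VAS for xerostomia was chosen as a primary outcome"), analysed as the change from week 0 to week 8.

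Two other inclusion criteria bear on the condition itself. Subjects must "have experienced xerostomia for 3 months prior to participation", and "the unstimulated salivary flow rates of the subjects should be under 0.3 mL/min".

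The Sample size calculation takes its planning values for the VAS from an earlier study: "A previous study demonstrated 1.54 points of improvement" relative to placebo, with an SD of 1.87. It does not say on what scale that study measured the VAS.

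**The concern.** One criterion appears with two values that differ tenfold, and the smaller one stands in the section that governs eligibility. A reader who takes that section together with the article's own scale definition arrives at an entry cut of 4 mm out of 100 mm.

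The VAS both admits subjects and measures the effect. Subjects who enter near the bottom of the scale have little room to fall. If enough of them were enrolled, the difference between groups would be diluted, and the population would not be the one the Abstract describes. Two centers recruit, and Trial status says that recruitment is under way, so the two figures could also be applied differently in practice.

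The planning values raise the same question of unit. A difference of 1.54 with an SD of 1.87 fits a 0-10 scale more naturally than a 0-100 mm scale, but the article does not say which applies.

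**Working it through.** **Inputs**

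- Threshold in the inclusion criteria: >4, no unit.
- Threshold in the Abstract: >40, no unit.
- Scale under Primary outcome: 0 to 100 mm. No 0-10 version is defined anywhere in the article.
- Planning values in the Sample size calculation: Δ = 1.54, σ = 1.87, power 80%, α = 5% with Z for α/2, ratio 1:1, dropout 25%.

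**Step 1: the thresholds as a share of the scale**

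| Reading | Share of range |
|---|---|
| >4 on 0-100 mm | 4/100 = 4% |
| >40 on 0-100 mm | 40/100 = 40% |
| >4 on 0-10 (not defined in the article) | 4/10 = 40% |

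The two written figures differ by 40/4 = 10. They agree only if >4 belongs to a 0-10 scale, which the reader has to supply. On the defined scale, subjects scoring above 4 mm and up to 40 mm are eligible under the inclusion criteria and ineligible under the Abstract.

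**Step 2: do the other criteria close the gap?**

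The 3-month criterion sets a duration without a severity. The flow limit is an objective measure. A subject scoring 5 mm with a 3-month history and a flow under 0.3 mL/min satisfies both, so neither supplies a minimum symptom score.

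**Step 3: room to improve**

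The scale ends at 0, so the largest possible fall equals the baseline value. A subject with a baseline of 5 mm can fall by at most 5 mm; one at 40 mm can fall by up to 40 mm. The floor matters most for the lowest scores and fades towards 40 mm.

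**Step 4: does the unit affect the sample size?**

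The article's formula with λ = 1 is n = 2(Zα/2 + Zβ)²σ²/Δ² per group.

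- As stated: 2 × (1.960 + 0.842)² × 1.87² / 1.54² = 23.2, so 24 per group.
- If the source used 0-10 (an assumption), Δ = 15.4 mm and σ = 18.7 mm: 2 × (1.960 + 0.842)² × 18.7² / 15.4² = 23.2, again 24 per group.

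Δ/σ = 1.54/1.87 = 15.4/18.7 = 0.82 in both cases, so converting the unit leaves n unchanged. The article's own figure of 36 per group is not reproduced by its formula and inputs, although the dropout step is: 36/(1 − 0.25) = 48 per group, 96 in total. That gap is a separate matter and has no bearing on the threshold.

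**The case against.** The strongest reply is that this is a slip of unit and does not describe two populations. The figure >4 has no unit, so 4 mm is a reading of it; on a 0-10 scale, >4 and >40 out of 100 are the same cut, and the planning values suggest that the authors had a 0-10 scale in mind. Sites also work from the full protocol and case report form, which are not shown, so the criterion actually applied may be sound. Both arguments have force, and the first is probably the true explanation. What remains is that the reader must override the only scale the article defines in order to reconcile its two statements of one entry criterion.

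A reader might infer more than the documents support, in four ways.

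- **That the trial is enrolling people with almost no xerostomia.** This rests on the literal 4 mm reading and leaves out the 3-month history and the flow limit. Such subjects would have a low symptom score but a reported history and a flow below the stated limit. The documents do not show that any have been enrolled.
- **That a subject entering at 5-15 mm could never show the planned effect.** The planning value is a difference from placebo between groups, and individual subjects are not required to reach it. The floor is a concern about dilution.
- **That the 2-week timing of the threshold contradicts the 7-day run-in** ("Before enrollment, all subjects will go through a 7-day run-in period"). The article describes a screening phase and lists the VAS at screening and at baseline as separate measurements. A screening score before the run-in is compatible with both statements, and the flow chart that could settle the timing is not available here.
- **That Δ and σ are 15.4 mm and 18.7 mm.** This depends on the scale of a source the article does not describe.

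**Conclusion.** The point holds as an internal inconsistency. The entry threshold on the primary-outcome scale is stated as >4 and as >40, without units, and the only defined scale is 0-100 mm. On that scale the inclusion criterion is set at 4% of the range against 40% in the Abstract. Taken literally, it would admit subjects with very low scores and little room to improve, and no other criterion prevents this.

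The contradiction itself needs no assumption. Its effect on the trial depends on whether the >4 figure was ever applied in millimetres, which the article cannot show; a mix of 0-10 and 0-100 units is the likelier cause. The missing scale for the planning values belongs to the same problem but does not alter the sample size. Correction is needed because eligibility rests on this figure and the change is small.

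**What to change.** 1. State one threshold, with its unit and on the 0-100 mm scale, in both the Abstract and the inclusion criteria. A cut of >40 mm is the reading that agrees with the Abstract and the Primary outcome section; the sponsor must confirm that it is the one intended.
2. Check the threshold and unit printed on the screening form, and compare the screening VAS of every subject already enrolled with the confirmed threshold.
3. In the Sample size calculation, state the scale of Δ = 1.54 and σ = 1.87. If the source used 0-10, add the equivalents of 15.4 mm and 18.7 mm.

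The cost is a wording correction and a check of existing screening records. The unit conversion calls for no new sample size.

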#### Safety

We will perform the following tests on all subjects at screening and after completion of YMJ administration: complete blood cell count; levels of aspartate aminotransferase/alanine aminotransferase, gamma-glutamyltranspeptidase, blood urea nitrogen, and creatinine; and erythrocyte sedimentation rate. These blood tests will help us to exclude subjects who have serious diseases and abnormal liver, heart, kidney, or other organ function. Throughout the present study, we will also check whether the 8-week administration of YMJ in xerostomia patients is safe by using these tests or CRF documentations.

In addition, at each visit, investigators will ask the subjects whether there are any adverse events (AEs) during the study period. If there is any AE, the investigator will provide the appropriate treatment to the subject immediately and record AEs in the dedicated document of the CRF including its severity and causality with the experimental agent. These AEs occurred during the entire study will be reviewed and monitored by independent CRA.

In the case of serious adverse events (SAEs), the investigator will offer the corresponding treatment to the subject immediately and report to IRB within 24 h from the time of recognition. If necessary, blind will be broken by adequate procedure and the documented procedure will be kept in the investigator study file.

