## Discussion

This clinical trial, which will be conducted as one of the nationwide projects to provide scientific evidence for TKM, belongs to the 2011 Traditional Korean Medicine R&D projects funded by the Ministry for Health & Welfare & Family Affairs, Republic of Korea.

The present study emphasizes the significance of treatment for xerostomia in the elderly, which has been neglected clinically up to this point, and can play an important role in giving prominence to treatment for this condition. We anticipate that this study will reveal that a herbal prescription and a typical TKM treatment method, YMJ, can be an alternative treatment for xerostomia in the elderly, a condition that presently has no suitable remedy.

In general, herbal medicine is a key tool of TKM treatment and is known to have a great curative power for many diseases
[35,36]. YMJ, which is one of the most frequently used herbal formulas in Korea, is regarded to be safe and to have a beneficial effect on xerostomia in the elderly
[21]. However, to our knowledge, no randomized controlled trials have shown the effectiveness of YMJ for xerostomia. Therefore, the current study was designed to obtain objective clinical evidence on the effects and safety of YMJ for the treatment of xerostomia in the elderly. If the effects of YMJ are verified in the present study, it could be used as a new alternative treatment option by elderly individuals with xerostomia, which is highly prevalent and without established standard therapies in conventional medicine.

The current study has three potential strengths. First, it is unique because the subjects of this study will have general xerostomia without the structural damage to the salivary glands that occurs with autoimmune disease or a history of radiation. Second, the ‘*Yin-deficiency*’ questionnaire, an indigenous pattern identification tool in TKM, will be applied to diagnose the subjects’ xerostomia according to TKM theory. If a high correlation is found between xerostomia in the elderly and ‘*Yin-deficiency*’, this will provide reasonable evidence for prescribing YMJ for xerostomia in the elderly. Third, we will determine whether YMJ can change the subjective feeling of dry mouth as well as the salivary flow rate. Although the relationship between a subjective feeling of dry mouth and the salivary flow rate is controversial
[8,9,37], the change in these factors in association with YMJ treatment could be compared in this study.

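### Exclusion (1) is tied to past treatment for autoimmune disease, so the criteria do not ensure the population without autoimmune gland damage that the Discussion describes

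*Protocol article*

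**What the plan says.** Under Inclusion and exclusion criteria, the exclusion list opens with "Subjects who report the following conditions will be excluded". Item (1) is "a history of treatments for autoimmune diseases like" Sjögren's syndrome, rheumatism or lupus. Item (2) is "a history of craniocervical radiation therapy, organ transplantation, severe psychiatric illness, or major depression". Item (4) is "the use of xerostomia-relieving medications (pilocarpine and cevimeline) or therapies for xerostomia", with mouthwash, gum and toothpaste as examples. On entry, the dryness VAS must be high and "the unstimulated salivary flow rates of the subjects should be under 0.3 mL/min".

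The Background says that recent xerostomia research has mostly dealt with Sjögren's syndrome or radiotherapy, "which are related to salivary gland damage", and that few studies cover elderly people without obvious structural damage. The Discussion then lists as the first potential strength that "the subjects of this study will have general xerostomia without the structural damage to the salivary glands that occurs with autoimmune disease"; it says the same of damage from earlier radiotherapy.

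Under Safety, the screening tests are a blood count, liver enzymes, urea nitrogen, creatinine and ESR, with the remark that "These blood tests will help us to exclude subjects who have serious diseases and abnormal liver, heart, kidney, or other organ function".

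**The concern.** The Discussion makes a statement about who will be enrolled, and exclusion (1) is the only criterion aimed at the autoimmune part of it. That criterion removes people by treatment history. Someone who has the disease but was never treated for it falls outside the exclusion and inside the population that the Discussion says is absent.

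The other entry rules do not work against this. Marked dryness and low unstimulated flow are what one would expect in a person with autoimmune gland disease, and recruitment is by open advertisement.

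Three things are at stake. One is whether the results can be generalized to elderly people without gland damage. Another is the set of Pearson correlations planned under Statistical analysis, between subjective and objective dryness and between dryness and the Yin-deficiency score. Subjects with damaged glands could move these in either direction, and the Discussion intends to use a high Yin-deficiency correlation as support for prescribing. The third, and smallest, is dilution of the treatment effect if such subjects respond less.

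**Working it through.** This is mainly a comparison of text. The question is whether a subject with known, never-treated Sjögren's syndrome would be stopped by any stated rule.

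1. **Exclusion (1).** It requires a history of treatment. The subject has none, so is not excluded.
2. **Exclusion (2).** It does not apply. It does show that the treatment wording is not a shorthand used throughout the list: severe psychiatric illness and major depression are named as conditions, with no requirement that they were treated.
3. **Exclusion (4).** It too works on the use of products. It removes some patients with known disease, but not one who uses none of them.
4. **Flow criterion.** It is an upper limit of 0.3 mL/min with no lower limit. The article defines hyposalivation as under 0.1 mL/min elsewhere, but eligibility does not use that figure. Very low flow does not exclude.
5. **Screening blood tests.** These are general. None is specific to autoimmune gland disease, and no rule links any of them, ESR included, to such a diagnosis.

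The subject is therefore eligible as written, and the criteria do not guarantee the Discussion's description.

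**Size.** The article gives no share of such subjects, so the effect cannot be computed from it. The following only bounds the dilution. Assume that a share f of each arm has gland disease and gains nothing at all. The expected difference becomes 1.54 × (1 − f). The difference of 1.54, the SD of 1.87 and the 36 per group come from Sample size calculation.

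- SE = 1.87 × √(2/36) = 0.44
- Power (two-sided 5%, normal approximation) = Φ(difference/SE − 1.96)

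| f (assumed) | Difference | Power |
|---|---|---|
| 0 | 1.54 | 94% |
| 5% | 1.46 | 91% |
| 10% | 1.39 | 88% |
| 20% | 1.23 | 80% |

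At f = 10%, 0.10 × 96 = 9.6, or about 10 of the 96 enrolled, would not fit the Discussion's description.

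The 36 per group is taken as printed. The article's formula with its own inputs gives (1.96 + 0.84)² × 1.87² × 2 / 1.54² ≈ 23.1, that is 24 per group, which is why power starts above the 80% target. That mismatch is a separate matter. The dropout step does reproduce: 36/0.75 = 48 per group, 96 in total.

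**The case against.** The strongest reply is that the gap is narrow and lies between a criterion and a Discussion remark. Much of this stands.

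- **Scope.** A reader might infer that the trial's formal question is xerostomia without gland damage. The Objectives and Hypothesis do not say so: they refer to xerostomia in the elderly without that qualifier. The restriction comes from the Background and the Discussion only.
- **Other screening.** A reader might infer that exclusion rests on self-report alone. Blood tests are also done at screening, and exclusion (4) removes users of dryness products. A subject with known disease would need to have been neither treated for it nor using such products. The gap is smaller for this, but not closed.
- **Shorthand.** In a condensed article the phrase may stand for known autoimmune disease, and investigators may apply it that way. This is possible, but the list names other conditions directly, and the article prints both the criterion and a claim that goes beyond it.
- **Bias and power.** A reader might infer a biased or underpowered comparison. Randomization should spread such subjects over both arms. Even with 20% complete non-responders, which nothing in the article suggests, power is about 80% with 36 per group.

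**Conclusion.** The point holds as a mismatch between the eligibility wording and the described population. Exclusion (1) leaves subjects with known, never-treated Sjögren's syndrome eligible, so the criteria do not ensure what the Discussion claims. One might go further and say that the trial will fail to enrol its described population. The article cannot show that: it gives no prevalence, and many diagnosed patients will have been treated and so excluded.

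The consequence is minor to moderate. It concerns the description of the population, generalizability and the interpretation of the correlations, with at most a modest dilution of the effect under the assumed shares above. Those shares, and the assumption of zero response, are illustrations and not estimates. The reading rests on the literal wording of the article, since the full protocol is not shown.

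**What to change.** Reconcile the two sections.

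1. Word exclusion (1) as a known diagnosis or history of Sjögren's syndrome, rheumatic autoimmune disease or lupus, whether or not treated. Suspected disease should not be added without a definition, because the sites could not apply it consistently.
2. Limit the Discussion claim to subjects without known autoimmune disease or craniocervical radiation. This is needed even after the first change, because no test specific to autoimmune gland disease is planned and undiagnosed disease can still enter.

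No new test is required. The cost is a few more screening exclusions and a minor amendment at both sites. Trial status says that recruitment is under way, so subjects enrolled before and after the amendment would have entered under slightly different wording, and the report should say so. If an amendment is not wanted, the second change alone would remove the contradiction but leave the gap in eligibility.
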